**Fig. 1 Fig1:**
[figure not shown]
Schedule of enrollment, interventions and assessments for the SPRING trial

### Study endpoint

The primary endpoint will be NIHSS score change within 4 h after general anesthesia by sevoflurane-remifentanil or propofol-remifentanil when observer’s assessment of alertness/sedation (OAA/S) reaches 4. The time to reach OAA/S score of 4 at the first time point will be recorded.

Secondary endpoints will be as follows:
The NIHSS score change at postoperative day 1 and postoperative day 2 from the baseline, the level of OAA/S in these two time points will be recorded.Hemodynamic stability including blood pressure, heart rate, episodes of hypertension, hypotension, tachycardia, and bradycardia;Intraoperative brain relaxation (Brain relaxation assessed immediately after opening of the dura on a scale ranging from 1 to 4 (1 = perfectly relaxed, 2 = satisfactorily relaxed, 3 = firm brain, 4 = bulging brain);Quality of anesthesia emergence including time of eye opening, time of emergence, coughing during extubation, postoperative nausea and vomiting (PONV), shivering, and agitation;Quality of anesthesia recovery assessed by QoR-40 at postoperative day 2;Changes of cognitive function at postoperative day 2 assessed by MMSE;Postoperative pain at PACU, 1, and 2 days after surgery evaluated by VAS;Postoperative neurological complications (e.g., intracranial hematoma, infection, seizure etc.);Anesthesia expenses and in-hospital total expenses;

### Data collection and management

Anesthesiologists on the follow-up team are all trained and received certification from the NIHSS official training program website (www.nihstrokescale.org). Data collection ends when patients are discharged from the hospital. All the information will be recorded on a Case Report Form (CRF), and raw, non-numerical data are coded for data storage, review, tabulation and analysis. Data will be entered at our medical center and stored and monitored securely in an electronic databases. Each of the data collection forms and the detailed information will be discussed on an item-by-item basis. Double data entry will be used, different data entering individuals will use standardized terminology and abbreviations, training will be performed regarding entering data on forms, and we will respond promptly to data discrepancy queries and general concerns about overall quality. Any missing data or errors in the data will be summarized along with detailed descriptions, and will be queried by checking the original forms. Data safety and monitoring inspectors will evaluate the trial safety, efficacy, and any ethical issues. The data to be collected and the procedures to be conducted at each visit will be reviewed in detail. There will not be a formal data monitoring committee (DMC) in this study, because the intraoperative anesthesia management is standard with minimal risks and the follow-up duration is short for this trial.

Paper case report forms are stored in numerical order and kept in locked cabinets. The electronic data will be saved in a database with password protection, and the passwords will be changed on a regular basis. Database backup will be performed once a month. All the original files will be maintained in storage for a period of 5 years after completion of the study.

### Participant retention

Once a patient is enrolled in the study, the team will make every effort to follow the patient for the entire study period. For patients whose consent is withdrawn, who are lost to follow-up, or discontinue for any reason, the reason will be recorded in the CRF in order to better interpret the results. The strategies that are used to improve participant retention are:
provide letters regarding the evaluation time schedule prior to data collection to remind patients and relatives of each assessment and test;provide adequate communication when visiting patients in the ward to let them be informed of upcoming data collection;limit patient burden related to follow-up visits to the greatest extent possible;patients who withdraw for follow-up assessment for one of the primary or secondary outcomes can continue with assessments for the other outcomes.

### Sample size calculation

Sample size calculation was conducted by PASS software (NCSS, LLC, USA). The mean difference of NIHSS change between the two types of anesthetics was estimated as 0.5, the estimated within group standard deviation was 1.5, and 1.0 was set as the equivalent margin based on clinical significance. Z-test was used as power analysis of equivalence tests of two independent proportions to detect equivalence. The minimum number of cases was 160 per group to achieve 80% power to detect a possible equivalence between the two groups. Considering the possibility of early termination during the study and allowing for a 10% drop-out rate, this number was raised to 176 subjects for each group. As two groups were to be studied, we aim to enroll 352 subjects.

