### Statistical analysis plan

Kolmogorov-Smirnov testing will be used for evaluating if the continuous variables have a normal distribution or not. Descriptive statistics will be reported as means with standard deviation for normally distributed data; medians with interquartile range will be described for non-normally distributed data; for categorical variables, count (percentage) will be described. The difference in postoperative NIHSS scores at certain time points between the propofol and sevoflurance groups will be analyzed by t-test or Mann-Whitney U test depending on normal or non-normal distribution, respectively, and 95% confident interval will be determined for the NIHSS score change and difference between the two groups. The changes in VAS scores, intraoperative parameters, and stress response biomarkers over the observation time will be compared using repeated measurement, and post hoc analysis will be used for sensitivity analysis. For other secondary outcomes such as brain relaxation, MMSE score, anesthesia quality score and medical expense, the difference between the two groups will be analyzed by t-test or Mann-Whitney U test. All the categorical variables will be analyzed by chi-square testing. Missing data will be adjusted using inverse probability weighting and worst-case imputation scenarios. Statistical significance is defined as a type I error of 0.05, and the nature of the testing is two-tailed. Analyses will be conducted using Statistical Package for the Social Sciences (SPSS) version 17.0 (Chicago, IL, USA).

All data will be analyzed according to an intent-to-treat, such that all randomized patients originally allocated to the propofol or sevoflurane anesthesia arm at the time of randomization will be used for efficacy analysis. No interim analysis is planned. Worst observation carried forward method will be used to handle missing data.

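### The sample-size paragraph names a two-proportions test and no alpha for an endpoint that is a mean, and 160 per group is more than the minimum for 80% power on its own inputs

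*Protocol article*

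**What the plan says.** The Study endpoint section of the Protocol article defines a score: "The primary endpoint will be NIHSS score change within 4 h after general anesthesia". The Study purpose section sets the equivalence range for the difference in score change at −1 to 1.

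The Sample size calculation section gives three inputs. The first is the assumed difference: "The mean difference of NIHSS change between the two types of anesthetics was estimated as 0.5". The second is an SD of 1.5 in each group. The third is an equivalence margin of 1.0 point, chosen on clinical grounds. It then names the method: "Z-test was used as power analysis of equivalence tests of two independent proportions to detect equivalence". The result is: "The minimum number of cases was 160 per group to achieve 80% power to detect a possible equivalence between the two groups". The drop-out step is "allowing for a 10% drop-out rate, this number was raised to 176 subjects for each group", which makes 352 in total. The paragraph gives no significance level.

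The Statistical analysis plan section compares NIHSS scores by t-test or Mann-Whitney test, plans a 95% confidence interval for the difference between groups, and adds: "Statistical significance is defined as a type I error of 0.05, and the nature of the testing is two-tailed".

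The Outcomes section says that NIHSS and mNIHSS will both be scored as primary outcomes. The Study endpoint section names NIHSS only.

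**The concern.** The paragraph contradicts itself. A mean difference, an SD and a margin in scale points are inputs to an equivalence test of two means. An equivalence test of two proportions needs two event rates and a margin on the rate scale, and it has no place for an SD. The article states no event rate for the primary endpoint.

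The result does not follow either. If 160 is called the minimum for 80% power, the inputs should return 160 at some level that the article states. Enrolment of 352 patients rests on this paragraph. A reader who cannot reproduce it cannot tell what power the trial has, or which equivalence rule the sample size was meant to support.

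**Working it through.** **Inputs.** Assumed difference d = 0.5, SD σ = 1.5, margin M = 1.0, power 80% and drop-out 10%, all from Sample size calculation; 1:1 allocation from Randomization and blinding. Alpha is not stated for the calculation. I take 0.025 per side, because concluding equivalence when a 95% interval lies inside −1 to 1 is the same as two one-sided tests at 0.025 each.

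**Step 1: the plan's own figures.** 160 × 1.10 = 176 and 2 × 176 = 352, so the drop-out step and the total can be traced. The 160 cannot.

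**Step 2: required n for two means.** With d on one side of zero, the nearer margin governs:

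n per group = 2σ²(z₁₋α + z₀.₈₀)² / (M − d)²

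2 × 1.5² / (1.0 − 0.5)² = 4.5 / 0.25 = 18

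- 0.025 per side: 18 × (1.960 + 0.842)² = 141.3, so 142. The t-based calculation gives 143.
- 0.05 per side, for comparison only: 18 × (1.645 + 0.842)² = 111.3, so 112.

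**Step 3: power at the stated n, 0.025 per side.**

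- 160 per group: the standard error is 1.5 × √(2/160) = 0.1677. Power = Φ(0.5/0.1677 − 1.960) = Φ(1.021) = 84.6%, or 84.4% with t. The far margin contributes essentially nothing.
- 158 per group: 84.2%, or 84.0% with t.

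**Step 4: can any nearby setting give 160?** None of those tried does.

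| Setting (per-side alpha) | n per group |
|---|---|
| 80% power, 0.05 | 112 |
| 80% power, 0.025 | 142 (t: 143) |
| 80% power, 0.0125 | 172 (t: 173) |
| 90% power, 0.05 | 155 |
| 90% power, 0.025 | 190 (t: 191) |
| β/2 formula, 80%, 0.05 | 155 |
| True difference 0, 80%, 0.025 | 48 |
| 142 with drop-out already included, 142/0.90 | 158 |
| 142 with Mann-Whitney efficiency 0.955 or 0.864 | 149 or 165 |

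For 160 to give exactly 80%, alpha would have to be about 0.016 per side, or the SD about 1.60 (at 0.025 per side) or 1.80 (at 0.05 per side). The article states none of these.

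**Step 5: drop-out.** To keep 160 after 10% loss takes 160/0.90 = 177.8, so 178. The planned 176 leaves 176 × 0.90 = 158.4, about 158. The gap is 2 per group and costs 0.4 percentage points of power (84.6% to 84.2%).

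**Step 6: sensitivity to the number of primary endpoints.** If alpha were split between NIHSS and mNIHSS (0.0125 per side, which the article does not state), 160 would give about 77% and 158 about 76%, and 80% would need 172 (t: 173).

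**The case against.** The best defence is that this is a labelling slip. Every input belongs to a means calculation, the software may have been run with the right procedure, and the article condenses a fuller document. That is plausible, and nothing shows that a proportions method produced the 160. But the sentence is a positive statement that conflicts with the inputs beside it, and correcting the label alone does not recover 160.

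Undisclosed settings might account for the number: drop-out counted once inside the 160 and again afterwards (158), or an efficiency allowance for the Mann-Whitney test (149 or 165). These are unstated and come only near 160. The first would also conflict with calling 160 a minimum to which drop-out is then added.

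Four stronger readings are tempting and are not supported.

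- *The trial is underpowered.* The error runs the other way: on the stated inputs 160 exceeds the 80% target.
- *The sample is 48 per group, or 43%, too large (160 against 112).* That needs a 90% interval rule, which appears nowhere in the article. Against the planned 95% interval the excess is 160 − 142 = 18 per group, about 13%.
- *The alpha is unknowable.* The sample-size paragraph does omit it, but the Statistical analysis plan section gives two-tailed 0.05 and a 95% interval, which point to 0.025 per side.
- *The drop-out formula invalidates the enrolment target.* The shortfall is 2 per group, and 158 is still above the 143 that the inputs require.

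**Conclusion.** The point holds as a defect in the stated justification, not as a shortage of patients. The named test does not fit the endpoint or the inputs, alpha is missing from the calculation, and 160 is not the minimum for 80% power. At 0.025 per side the inputs need 142 per group (143 with t); 160 gives about 84%, as does the 158 left after 10% drop-out from 176.

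This rests on the article's own difference, SD and margin, and on reading the 95% interval as the equivalence rule. It applies to NIHSS change alone. If mNIHSS is also primary, as the Outcomes section says, the 84% cannot be claimed without qualification: under an alpha split power would fall to about 76–77%. If equivalence had to be shown on both scales without a split, joint power could not exceed that for NIHSS alone, and the article gives no mNIHSS inputs from which to compute it.

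**What to change.** Keep 352 patients, delete the reference to proportions, and replace the calculation with text such as:

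> Two one-sided tests for two means, margin ±1.0, assumed difference 0.5, SD 1.5, alpha 0.025 per side (equivalence if the 95% CI lies within −1 to 1). 143 evaluable per group give 80% power. 176 randomized per group leave about 158 evaluable after 10% drop-out and give about 84% power for the NIHSS change as the single primary endpoint.

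Then reconcile the Outcomes section with the Study endpoint section. Either make NIHSS change the only primary endpoint, or state how alpha and power are handled for two. Stating power at the expected 158 evaluable also disposes of the drop-out point, so 176 need not become 178.

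The cost is one paragraph and one consistent statement of the primary endpoint. Enrolment does not change if NIHSS change is the single primary endpoint.

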### Statistical analysis plan

Kolmogorov-Smirnov testing will be used for evaluating if the continuous variables have a normal distribution or not. Descriptive statistics will be reported as means with standard deviation for normally distributed data; medians with interquartile range will be described for non-normally distributed data; for categorical variables, count (percentage) will be described. The difference in postoperative NIHSS scores at certain time points between the propofol and sevoflurance groups will be analyzed by t-test or Mann-Whitney U test depending on normal or non-normal distribution, respectively, and 95% confident interval will be determined for the NIHSS score change and difference between the two groups. The changes in VAS scores, intraoperative parameters, and stress response biomarkers over the observation time will be compared using repeated measurement, and post hoc analysis will be used for sensitivity analysis. For other secondary outcomes such as brain relaxation, MMSE score, anesthesia quality score and medical expense, the difference between the two groups will be analyzed by t-test or Mann-Whitney U test. All the categorical variables will be analyzed by chi-square testing. Missing data will be adjusted using inverse probability weighting and worst-case imputation scenarios. Statistical significance is defined as a type I error of 0.05, and the nature of the testing is two-tailed. Analyses will be conducted using Statistical Package for the Social Sciences (SPSS) version 17.0 (Chicago, IL, USA).

All data will be analyzed according to an intent-to-treat, such that all randomized patients originally allocated to the propofol or sevoflurane anesthesia arm at the time of randomization will be used for efficacy analysis. No interim analysis is planned. Worst observation carried forward method will be used to handle missing data.

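### The NIHSS test is stated on postoperative scores although the endpoint, the ±1 hypothesis and the sample size are on change from baseline, and the plan does not say which analysis decides equivalence

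*Protocol article*

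**What the plan says.** **Endpoints (Study endpoint).** The primary endpoint is a change: "The primary endpoint will be NIHSS score change within 4 h after general anesthesia by sevoflurane-remifentanil or propofol-remifentanil". So are the later NIHSS endpoints, "The NIHSS score change at postoperative day 1 and postoperative day 2 from the baseline", and the cognitive endpoint, "Changes of cognitive function at postoperative day 2 assessed by MMSE".

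**Hypothesis and sample size.** Study purpose puts the equivalence hypothesis on NIHSS (or mNIHSS) score changes, with a difference between -1 and 1. Sample size calculation is on the same scale: "The mean difference of NIHSS change between the two types of anesthetics was estimated as 0.5", with an SD of 1.5 and a margin of 1.0.

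**Analysis (Statistical analysis plan).** The test clause reads "The difference in postoperative NIHSS scores at certain time points between the propofol and sevoflurance groups will be analyzed by t-test or Mann-Whitney U test". The sentence ends by promising that a "95% confident interval will be determined for the NIHSS score change and difference between the two groups". MMSE appears in a list: "For other secondary outcomes such as brain relaxation, MMSE score, anesthesia quality score and medical expense", again to be compared by t-test or Mann-Whitney U test. The section does not mention adjustment for the baseline score.

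**Data.** The Outcomes section has both NIHSS/mNIHSS and MMSE measured at baseline and after operation.

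**The concern.** One sentence names two variables for the primary comparison: the postoperative score for the test and the change for the interval. A statistician who follows the test clause would analyse something other than the endpoint, with no use of a baseline that is already collected. If the two analyses disagree, the text gives no rule.

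The interval clause can also be read in two ways. It may mean an interval for the between-group difference in change. It may instead mean a within-group interval for change plus an interval for the between-group difference in postoperative score, since that is the only difference the sentence has named up to that point. The analysis section never connects either interval to the margin of 1, which is what an equivalence conclusion needs.

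Pre-existing deficit is possible in this population. Table 1 requires a Glasgow score of 15 and the ability to cooperate, and admits recurrent glioma, but sets no upper limit on baseline NIHSS. A patient with a stable preoperative deficit can score high after surgery with zero change. In a comparison of raw postoperative scores, that spread between patients is part of the noise.

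**Working it through.** **1. The plan's own figure.** Inputs from Sample size calculation: margin 1.0, expected difference 0.5, SD 1.5, 80% power. For equivalence of two means, n per group = 2 × SD² × (z_α + z_β)² / (margin − difference)².
- One-sided 0.025: 2 × 2.25 × (1.960 + 0.842)² / 0.25 = 142.
- One-sided 0.05: 2 × 2.25 × (1.645 + 0.842)² / 0.25 = 112.

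Neither gives the stated 160. With 160 per group the power is about 84% (one-sided 0.025) or 91% (one-sided 0.05). That mismatch is a separate matter. Here 160 per group is taken as given and a 95% interval is used.

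**2. Expected difference.** Postoperative score = baseline + change. Randomization makes the expected baseline equal in the two arms, so the expected group difference is the same for the raw score and for the change. Only the precision and the chance imbalance differ.

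**3. Scenario A: change independent of baseline (assumption).** Baseline SD b is assumed, because the document gives none. Raw SD = √(1.5² + b²); SE = SD × √(2/160); chance that the 95% interval lies within ±1 at a true difference of 0.5 ≈ Φ(0.5/SE − 1.96).

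| Variable | SD | SE | Chance within ±1 |
|---|---|---|---|
| Change | 1.50 | 0.168 | 0.846 |
| Raw, b = 0.5 | 1.58 | 0.177 | 0.807 |
| Raw, b = 1 | 1.80 | 0.202 | 0.699 |
| Raw, b = 2 | 2.50 | 0.280 | 0.432 |

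Exact t-based values are at most 0.3 percentage points lower. The 95% range of the chance baseline imbalance is ±1.96 × b × √(2/160) = ±0.11, ±0.22 and ±0.44 point for b = 0.5, 1 and 2. This is the same variance seen from another side and should not be counted as a second loss.

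**4. Scenario B: equal baseline and postoperative SD s, correlation r (assumption).** Change SD = s√(2(1 − r)). Holding it at 1.5 gives raw SD s = 1.5/√(2(1 − r)). With baseline as covariate, the large-sample residual SD is s√(1 − r²) = 1.5 × √((1 + r)/2).

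| r | Raw SD | Chance within ±1, raw (t-based) | Baseline-adjusted SD |
|---|---|---|---|
| 0.3 | 1.27 | 94% | 1.21 |
| 0.5 | 1.50 | 84% | 1.30 |
| 0.7 | 1.94 | 63% | 1.38 |
| 0.9 | 3.35 | 24% | 1.46 |

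On change the t-based figure is 84% throughout. The raw score is therefore worse than change only above r = 0.5, equal at 0.5, and better below it. The baseline-adjusted SD is below both the raw SD and 1.5 in every row. In scenario A it equals 1.5, the SD of change.

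**The case against.** The best defence is that the plan does analyse change. Its NIHSS sentence ends with a 95% interval for the score change, and in an equivalence trial an interval set against the margin is what can settle the question. On that reading the test clause is shorthand: Study purpose uses nearly the same phrase with the word for changes included. This stands in part. The change endpoint is not left out for NIHSS, and the losses in scenario A apply only if the deciding interval is built on the raw score. The ambiguity remains, because the sentence uses the word change for one quantity and not for the other and does not say which one is set against ±1.

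A reader might infer that preoperative deficits bias the comparison. The document does not support this, since 1:1 randomization balances them in expectation. Nor does it support a certain loss of power. No baseline SD or correlation is given, and at a low correlation the raw score does better. Exclusions such as insular invasion, neuromuscular disease and scheduled motor evoked potential monitoring may also narrow the baseline spread, which makes the 43% figure an extreme case and not a forecast. At an assumed baseline SD of 0.5, the raw score still reaches about 81%.

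The MMSE part is weaker. The score stands in a list that names instruments, and Study endpoint already fixes change, so this is unclear wording and not an explicit choice of the raw score.

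Finally, baseline adjustment goes beyond inserting the word change. That is true, and its cost is stated below.

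**Conclusion.** The inconsistency is real and lies within the document shown: the test is named on postoperative scores, while the NIHSS endpoints, the ±1 hypothesis and the sample size are on change. The interval clause softens it but does not resolve it, because neither the deciding analysis nor the link to ±1 is stated. For MMSE the analysed variable is unclear.

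The consequence is chance imbalance and a possible loss of precision, without bias. Its size cannot be fixed from the document. It ranges from a gain at low correlation to a substantial loss: from about 85% to 43% under scenario A with an assumed baseline SD of 2, or from 84% to 24% under scenario B with r = 0.9. All figures assume 160 per group, a true difference of 0.5, a change SD of 1.5 and a 95% interval. The correction is worth making because it removes the ambiguity and, in large samples, is at least as precise as either alternative at any correlation.

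**What to change.** In the Statistical analysis plan section:
- Name NIHSS change from baseline, and mNIHSS change likewise, as the analysed variable at each time point.
- Estimate the between-group difference with the baseline score as covariate.
- State that the confidence interval for this difference in NIHSS change is judged against -1 to 1 and that this decides equivalence.
- Analyse MMSE change from baseline in the same way, without a margin.

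The cost is small. A baseline-adjusted model replaces the simple t-test or Mann-Whitney U test as the main analysis; those can stay as supporting analyses of change. Both baselines are already collected, and the planned number is unaffected because it is already stated on change.

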## Methods

### Study purpose

(1) Primary purpose: To investigate neurologic function in the early postoperative period for patients with supratentorial intracranial gliomas under inhalational general anesthesia compared to intravenous general anesthesia. The hypothesis is that the difference in postoperative National Institute of Health Stroke Scale (NIHSS or modified NIHSS) score changes under the two general anesthesia methods are not different, with the score difference within − 1 to 1.

(2) Secondary purpose: To compare the effects of inhalational general anesthesia versus intravenous general anesthesia on neurocognition, hemodynamics, cerebral physiology, anesthesia recovery quality, pain scores, anesthesia expenses, and stress responses in patients with supratentorial intracranial gliomas undergoing elective craniotomy.

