#### Outcomes

Patients will have been screened 1 to 2 days before operation, and the demographic characteristics, clinical manifestations, and past history obtained at this time. Detailed descriptions of the lesion in MRI will be obtained. The lesions’ pathologic diagnoses will be obtained 2 weeks after the tumor removal. Neurologic function will be assessed using the National Institute of Health Stroke Scale (NIHSS/mNIHSS) at baseline and in the postoperative period. NIHSS scores 15 items including consciousness, visual function, facial and motor function, ataxia, sensory and language function, and attention, and the total score ranges from 0 (no deficit) to a maximum of 42. A modified version of the NIHSS (mNIHSS) abridges to 11 items by deleting level of consciousness, facial palsy, limb ataxia, and dysarthria; the sensory item is collapsed from 3 to 2 choices [15]. Since there is no reliability and validity evidence comparing NIHSS and mNIHSS use in the intracranial tumor population, we will score both as primary outcomes in this study. The scoring system is shown in appendix. Mini-mental state examination (MMSE) will be used to assess the cognitive performance of patients at baseline and after operation. During anesthesia recovery, Anesthesia Recovery Quality and the modified Aldrete scale will be used to assess the recovery condition of patients. Visual Analog Scale (VAS) will be used to assess postoperative pain. QoR-40 (Quality of Recovery from Anesthesia) will be used at 2 days after operation to assess the recovery condition and the satisfaction of the patient related to anesthesia. All adverse events will be recorded. The schedule of data collection is shown in Fig. 1.

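### The primary NIHSS comparison makes no adjustment for the baseline NIHSS that the trial collects, giving up precision against the ±1 margin at no saving

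*Protocol article*

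**What the plan says.** The Outcomes section plans the baseline measurement: "Neurologic function will be assessed using the National Institute of Health Stroke Scale (NIHSS/mNIHSS) at baseline and in the postoperative period". It does the same for cognition: "Mini-mental state examination (MMSE) will be used to assess the cognitive performance of patients at baseline and after operation". The Study endpoint section makes the NIHSS change within 4 h, when OAA/S reaches 4, the primary endpoint. The Study purpose section states the equivalence hypothesis "with the score difference within − 1 to 1".

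The Statistical analysis plan section says of the postoperative NIHSS scores in each arm that they "will be analyzed by t-test or Mann-Whitney U test depending on normal or non-normal distribution, respectively, and 95% confident interval will be determined". That interval is to cover both the change in score and the difference between arms. MMSE and several other secondary outcomes get the same choice of t-test or Mann-Whitney test. No covariate, ANCOVA or regression model is named for NIHSS or MMSE anywhere in the article. The Randomization and blinding section describes 1:1 allocation in blocks of 4 and states no stratification factor.

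**The concern.** In an equivalence trial the claim rests on whether the interval for the difference fits inside the margin, so the width of that interval matters directly. The baseline NIHSS is likely to predict the postoperative score, because both new and recurrent gliomas are eligible and patients may enter with existing deficits. The plan has this value in hand but gives it no role beyond, at most, subtraction.

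Subtracting baseline is not the same as adjusting for it. A change score fixes the slope of postoperative on baseline NIHSS at 1. If the true slope is smaller, subtraction over-corrects: it adds baseline noise to the outcome, and an arm that happens to start worse will appear to change less. Nothing in the randomization balances the arms on baseline deficit. The sample size section assumes a true difference of 0.5 against a margin of 1, so only 0.5 point separates the expected estimate from the margin.

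**Working it through.** **Inputs from the Sample size calculation section**
- True difference 0.5: "The mean difference of NIHSS change between the two types of anesthetics was estimated as 0.5".
- SD and margin: "the estimated within group standard deviation was 1.5, and 1.0 was set as the equivalent margin based on clinical significance". The SD is read as that of the NIHSS change.
- Size: "The minimum number of cases was 160 per group to achieve 80% power to detect a possible equivalence between the two groups".
- Two-sided type I error 0.05 and a 95% interval, from the Statistical analysis plan section.

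**Assumptions not in the document.** ρ is the correlation between baseline and postoperative NIHSS. k is the baseline SD divided by the postoperative SD. Both are varied below.

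**The plan's own figure.** When the true difference is 0.5, the nearer limit governs:

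n per group = 2 × [1.5 × (z₁₋α + 0.842) / (1 − 0.5)]²

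This gives 141.3, so 142, with α = 0.025 per side (95% interval), and 111.3, so 112, with α = 0.05 per side (90% interval). The stated 160 is not reproduced. That is a separate matter; the stated 160 is used from here on.

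**Power of the unadjusted change comparison**

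SE = 1.5 × √(2/160) = 0.1677

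Power = Φ(0.5/SE − z) + Φ(1.5/SE − z) − 1

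- 95% interval (z = 1.96): 84.6%, half-width 0.329.
- 90% interval (z = 1.645): 90.9%.

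**Effect of adjustment.** In large samples:

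Var(ANCOVA) / Var(change) = (1 − ρ²) / (1 + k² − 2ρk)

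This reduces to (1 + ρ)/2 when k = 1. At ρ = 0.5 and k = 1 the ratio is 0.75, the effective SD is 1.5 × √0.75 = 1.299, the SE is 0.1452 and the half-width is 0.285. Power is 93.1% with a 95% interval and 96.4% with a 90% interval.

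95% interval, 160 per group, gain over 84.6%:

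| k | ρ | Variance ratio | Power | Gain (points) |
|---|---|---|---|---|
| 1 | 0.3 | 0.65 | 95.9% | +11.2 |
| 1 | 0.5 | 0.75 | 93.1% | +8.4 |
| 1 | 0.7 | 0.85 | 89.9% | +5.2 |
| 1 | 0.8 | 0.90 | 88.2% | +3.5 |
| 1 | 0.9 | 0.95 | 86.4% | +1.8 |
| 0.75 | 0.3 | 0.82 | 90.9% | +6.3 |
| 0.75 | 0.5 | 0.92 | 87.4% | +2.7 |
| 0.75 | 0.7 | 1.00 | 84.8% | +0.2 |
| 0.5 | 0.3 | 0.96 | 86.1% | +1.5 |
| 0.5 | 0.5 | 1.00 | 84.6% | 0.0 |
| 0.5 | 0.7 | 0.93 | 87.2% | +2.6 |

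Gains are differences of unrounded powers. The gain is zero exactly when ρ = k, because the true slope ρ/k is then 1. Simulation at k = 1 (4,000 trials per value of ρ, 160 per arm) agreed, change against ANCOVA: 84.8% against 92.9% at ρ = 0.5, 84.9% against 89.5% at 0.7, and 84.5% against 86.1% at 0.9.

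**Chance imbalance.** At k = 1 the SD of each score is 1.5/√(2(1 − ρ)): 1.50 at ρ = 0.5 and 1.94 at ρ = 0.7. A baseline imbalance of 1.96 standard errors is then 0.329 or 0.424 point. The change-score estimate shifts by (1 − ρ) times that:
- ρ = 0.5: 0.5 × 0.329 = 0.16 point.
- ρ = 0.7: 0.3 × 0.424 = 0.13 point.

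These are about a third and a quarter of the 0.5 point of room. The adjusted estimate removes this shift when the linear model holds.

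**The case against.** The strongest reply is that nothing here is invalid. Under randomization an unadjusted comparison of change is unbiased and its interval has nominal coverage. That stands. So does the observation that, on the plan's own inputs, the unadjusted analysis already has 84.6% power against a target of 80%.

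The size of the gain is also uncertain. Eligibility requires a Glasgow score of 15 and excludes patients with impaired mental status or who cannot cooperate with the examination. Baseline scores may therefore vary less than scores taken within hours of a craniotomy, and the table shows the gain can then be small or nil. That stands too, and no single figure should be read as the expected gain.

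Chance imbalance is not a harm on top of the wider interval. Averaged over randomizations it is already part of the sampling variance; the 0.16 and 0.13 are shifts conditional on an unlucky allocation. Regression to the mean affects both arms equally in expectation and does not bias the difference.

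Two further replies carry less weight. An interval could in principle come from an adjusted model, but the article names none and pairs the interval with two tests that have no place for a covariate. A separate analysis plan might adjust, but the article's own analysis section states the method for NIHSS, and the point is about that stated method.

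**Conclusion.** The concern holds as a point of efficiency and of sensitivity to chance imbalance, not of validity. Baseline NIHSS is collected, the stated primary comparison does not adjust for it, and no reason is given. On the plan's inputs with 160 per group and a 95% interval, adjustment gains 8.4 points of power at ρ = 0.5 with equal SDs. Across the values tabulated the gain runs from 0 to 11.2 points. It rests on ρ and k, which the protocol does not report, and on reading the SD of 1.5 as that of the change. In large samples adjustment never costs precision. The unadjusted plan does not fall below its 80% target, so the change is worth making but the trial does not fail without it. The day 1 and day 2 NIHSS comparisons and the day 2 MMSE comparison have the same gap.

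**What to change.** In the Statistical analysis plan section, make the primary analysis a linear model of the NIHSS change at the first OAA/S 4 assessment on treatment arm and baseline NIHSS. Use a robust or bootstrap standard error, because the score is an integer and likely to be skewed. Compare the confidence interval of the adjusted mean difference with −1 to +1, and keep the unadjusted difference as a supporting result. With baseline in the model, the treatment estimate is the same whether the outcome is the postoperative score or the change. Use the same form for NIHSS on days 1 and 2, and for MMSE on day 2 with baseline MMSE.

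The cost is a sentence or two of wording and one degree of freedom per model. No new data or patients are needed, and because the estimate is still a mean difference in NIHSS change, the margin and the sample size can stay. The choice must be fixed before the data are analysed; added later in an open-label equivalence trial, it could look driven by the results.
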